## Methods: assignment of interventions

### Allocation sequence generation

Participants are randomly allocated to either the intervention group or control group in blocks of 8 and stratified by age (<75 or ≥75 years of age), sex, and municipality. A random 1:1 sequence of two letters was generated for each block, with the statistical software R 3.6.0 (R Foundation for Statistical Computing, Vienna, Austria) using the sampling function. The randomization sequence was generated by a statistician uninvolved in the trial, and who was unaware of which letter was assigned to which group.

### Allocation concealment mechanisms and implementation

Allocation concealment is achieved as the person performing patient recruitment and data collection (blinded) does not have access to the randomization sequences and is not involved in the randomization. Persons not involved in recruitment will inform intervention staff and participants about group allocation, based upon the randomization sequence. The randomization is performed immediately after a participant has consented to participate and is based solely on stratification-relevant data. The staff performing the interventions (unblinded) are informed immediately after randomization. Participants are informed after baseline data has been collected.

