**Fig. 2 Fig2:**
[figure not shown]
Schematic overview of the MULTI-NUT-MED and MED intervention elements and their timeframe. X indicates the timepoint of the intervention element. *These interventions are provided on an individually assessed need. Thus, only the possible timespan of the intervention is indicated. Abbreviations: Multidisciplinary (MULTI), Nutrition (NUT), Medication (MED), and Activities of Daily Living (ADL)

**Table 1 Tab1:** A schematic overview of the study design. Definition of timepoints: t_1_: Within 36 h after admission the ED, t_a_: Immediately after data collection upon enrollment has ended, t_GFR_: During hospitalization or up to 2 weeks after discharge, t_2_: 8 weeks after discharge, t_3_: 16 weeks after discharge, t_1y_: 1 year after discharge. Abbreviations: *GFR* glomerular filtration rate, *MULTI* multidisciplinary, *NUT* nutritional, *MED* medication

Timepoint	Enrollment	Allocation	Post allocation			Close-out
	t_1_	t_a_	t_GFR_	t_2_	t_3_	T_1y_

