### Eligibility criteria, recruitment, and consent

Patients are eligible for inclusion if they are ≥65 years of age, acutely admitted to the ED, community-dwelling, and residing in one of the following municipalities: Hvidovre, Copenhagen (Districts of West and South Western Copenhagen), or Brøndby. Exclusion criteria are inability to understand Danish, inability to cooperate physically (e.g., hearing or speech impairment), or cognitively (e.g., dementia or unconsciousness), isolation room stay, not Caucasian, and admission due to suicide attempt or terminal illness.

Participants are recruited up to 36 h after admission. Each morning (Monday through Thursday), patients are assessed for eligibility from a randomized computer-generated list of all patients in the ED. Eligible patients are informed about the trial both verbally and in writing by a team of seven researchers and are given the possibility of a reflection period of 24 h to consent to participation. Participants are given the option to consent separately to GFR measurement and pharmacogenetic test. After obtaining written informed consent, each participant is randomized to either the intervention group or standard care, and baseline data are collected. After baseline data are collected, each participant is informed about the result of the randomization by staff performing the intervention.

The following strategies are implemented to minimize the effect of staff shortages on patients recruitment: (1) on days with insufficient hospital staff available to perform the MULTI-NUT-MED intervention, only patients with a Mini Nutritional Assessment Short-Form (MNA-SF) [60] score >11 are recruited (to the MED intervention only); (2) on days with insufficient community-based staff available to perform future nutritional intervention (e.g., due to vacation or long term illness), patients from these municipalities are not assessed for eligibility; (3) if more than 35% of the first 50 included patients (*n* = 50) have an MNA-SF score >11, then the project leaders can decide to exclusively recruit patients with an MNA-SF score ≤11 2 days of each week in order to achieve a sufficient number of participants with an MNA-score ≤11 (see the “Sample size” section). The expected recruitment rate is two participants per week for 100 weeks.

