### Interventions

The intervention is individualized: participants in the intervention group without malnutrition (MNA-SF >11) only receive the MED intervention, and participants in the intervention group with or at risk of malnutrition (MNA-SF ≤11) receive the MULTI-NUT-MED intervention (see Fig. 1 and Table 1).

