##### During hospitalization

Immediately after randomization, the research dietitian creates a dietary plan in collaboration with the participant for the participant to follow during hospitalization. This dietary plan is based on foods and nutritional products available at the hospital as well as the participant’s nutritional needs [70], self-reported food preferences, and ability to chew (oral or dental pain and masticatory difficulties) and swallow (evaluated by the EAT-10 score [71, 72] and an occupational therapist).

Foods and nutritional products available at the hospital include a fixed menu in the ED or an *a la carte* menu in specialized wards, energy- and protein-enriched or texture-modified menus, oral nutritional supplements (ONS), and a selection of beverages and in-between meals. Participants in the MULTI-NUT-MED intervention may also receive P-Boost®(Adosan), a fluid protein-only supplement.

Daily dietary intake is recorded in a food diary by the participant and validated by the research dietician the following day. If a food diary is incomplete, then the research dietician performs a 24-h dietary recall [73]. Both dietary intake and dietary plans are entered in VITAKOST [74]. If 100% of energy and protein and energy requirements is not achieved on a given day, then the dietary plan is adjusted for the following day. If >75% of protein and energy requirements is not achieved for 2 days in a row, then tube feeding or parenteral nutrition is advised in collaboration with the medical doctor.

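### The article gives two orders for randomization and baseline assessment, so the MNA-SF class and baseline EuroQol-5D-5L used for the quality-of-life endpoint are not clearly fixed before unblinded staff know the allocation

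*Protocol article*

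**What the plan says.** The protocol article describes the sequence in four places.

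- **Table 1** defines the allocation time point t_a as "Immediately after data collection upon enrollment has ended". Nutritional screening and baseline quality of life are at the enrollment time point t_1.
- **Eligibility criteria, recruitment, and consent** says that, once consent is written, "each participant is randomized to either the intervention group or standard care, and baseline data are collected".
- **Allocation concealment mechanisms and implementation** says "The randomization is performed immediately after a participant has consented to participate and is based solely on stratification-relevant data". It continues: "The staff performing the interventions (unblinded) are informed immediately after randomization", and "Participants are informed after baseline data has been collected".
- **Dietary counseling, During hospitalization** says "Immediately after randomization, the research dietitian creates a dietary plan in collaboration with the participant".

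Two further statements show what depends on this order. Under Interventions, "participants in the intervention group with or at risk of malnutrition (MNA-SF ≤11) receive the MULTI-NUT-MED intervention", and the third sample-size calculation and the EuroQol-5D-5L analysis concern that same group. Under Allocation sequence generation, randomization is "stratified by age (<75 or ≥75 years of age), sex, and municipality", so the MNA-SF score is not needed to randomize.

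**The concern.** A baseline measure protects a randomized comparison only if allocation cannot influence it. Two baseline measures carry the third primary endpoint. MNA-SF ≤11 decides who is in the analysis, and baseline EuroQol-5D-5L is the covariate in the ANCOVA. Several MNA-SF items and the whole of EuroQol-5D-5L depend on what the participant reports.

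If allocation exists and intervention staff know it before these are recorded, staff contact could hint at the group and shift either measure in one arm. A shifted covariate carries over into the adjusted difference. A shifted MNA-SF changes who is compared.

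There is also a plain bookkeeping gap. Someone randomized at consent who withdraws, dies or is discharged before baseline has been assigned a group but has no MNA-SF score. The intention-to-treat population for this endpoint then has no rule that places them inside or outside it.

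**Working it through.** No figure in the plan depends on the order of events, so the check sets the statements side by side.

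**Step 1: the order in each place**

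| Place | Order given |
|---|---|
| Table 1 | consent and enrollment data (including nutritional screening and quality of life), then allocation |
| Eligibility section | consent, randomization, baseline data, participant informed |
| Allocation concealment section | consent, randomization, intervention staff informed at once; participant informed after baseline |
| Dietary counseling section | randomization, then at once a plan made with the participant |

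The first row cannot be true together with the second and third. The fourth fits the first. With the second and third it fits only if the participant meets the dietitian before baseline is complete, and the third row is meant to prevent disclosure at that stage.

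**Step 2: is the dietitian's step workable under the order in the text?** The hospital dietary plan draws on the EAT-10 score, which Table 2 lists at t_1. It belongs to the MULTI-NUT-MED package, given only at MNA-SF ≤11. The multidisciplinary intervention section bases the choice of elements on screening done during baseline collection. So the dietitian needs baseline results first. Either randomization in practice follows baseline, as in Table 1, or the dietitian's contact does not come directly after randomization. The article does not say which.

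**Step 3: which participants are affected?** The Eligibility section restricts recruitment by MNA-SF in two situations: scores above 11 only on days short of hospital staff, and scores of 11 or below only on two days a week if the project leaders invoke that rule. On those days the score must be known before recruitment. Days limited to scores above 11 contribute nobody to the third endpoint. The MNA-SF part of the concern therefore applies to unrestricted days. The EuroQol-5D-5L part applies to every day that contributes participants to the endpoint.

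**Step 4: does the missing-data plan close the membership gap?** The Statistical methods section imputes the missing primary endpoint from earlier measurements, age, sex and diagnosis codes. It fills in an outcome for a person already in the population. It does not assign an MNA-SF class.

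**Step 5: can the change still affect conduct?** The trial started on 15 October 2018. Two participants a week for 100 weeks gives 2 × 100 = 200, so recruitment was planned to end about September 2020, a year before the article appeared in September 2021. Unless recruitment ran late, what remains is reporting and analysis.

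**The case against.** The strongest reply is that the safeguards are already stated. The person who recruits and collects data is blinded, has no access to the sequences and takes no part in randomization. The outcome assessor is blinded throughout. Two sections say that participants learn their group only after baseline. The medication review starts once baseline data are available, and the dietary plan needs the EAT-10 score. Read together, these suggest that staff contact follows baseline and that t_a in Table 1 marks disclosure rather than randomization.

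Much of this stands. A reader might infer that baseline was assessed open-label. The documents do not support that: what remains is a possible leak through unblinded staff. The disclosure reading of t_a is possible, but the row is labelled as allocation and the concealment section treats randomization and disclosure as separate events. The article therefore still gives two orders.

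Two other inferences go too far. One is a numerical bias in the EuroQol-5D-5L difference: it would need the size of a baseline shift and the covariate slope, and the documents give neither. The other is that leaving MNA-SF out of the stratification undermines the equal allocation assumed for the 130 participants. Simulation with 200 participants, 12 equal strata (two age groups, two sexes, three municipalities), blocks of 8 and 65% at MNA-SF ≤11 puts the arm difference within about 14 in 95% of runs, for example 58:72. The effective sample size is then 4 × 58 × 72 / 130 = 128.5, a loss of about 1%. That gives no reason to change strata or block size.

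**Conclusion.** The inconsistency is certain and bears on a primary endpoint. Table 1 and the text give opposite orders for allocation and baseline, and the dietitian's step, read literally after randomization at consent, conflicts with withholding the allocation from participants until baseline is done. Under the order in the text, MNA-SF (on unrestricted days) and baseline EuroQol-5D-5L can be recorded after unblinded staff know the group, and a participant lost before baseline cannot be placed in or out of the endpoint-3 population.

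The harm is possible rather than shown. It rests on two assumptions: that the order in the text was the one followed, and that contact with unblinded staff before baseline conveyed the group. If Table 1 describes what happened, nothing is wrong beyond the wording. The size of any bias cannot be derived from the article. The point should be settled because it touches a primary endpoint and settling it costs little.

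**What to change.** **Text.** Reconcile Table 1, the Eligibility section, the Allocation concealment section and the hospital part of Dietary counseling to one order. MNA-SF, EuroQol-5D-5L and the other baseline data should be completed and locked before randomization, or at minimum before the allocation is released to intervention staff or anyone else in contact with the participant. This also gives every randomized participant a known MNA-SF class if randomization itself waits for baseline.

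**Participants already enrolled.**
- Report the time order of baseline completion, release of the allocation to staff and first intervention contact.
- Report, by arm, any randomized participants without an MNA-SF score.
- Run a sensitivity analysis of the EuroQol-5D-5L endpoint that excludes participants whose MNA-SF or baseline EuroQol-5D-5L was recorded after first contact with intervention staff. Give the number excluded by arm. Such contact is likelier in the intervention arm, so the result is supportive only.

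**Cost.** A few sentences, one table of timings and one extra analysis, with no new data if time stamps were kept. For any participant still to be enrolled, randomization happens slightly later. The stratification factors, block size and municipality grouping can stay as they are.

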### Blinding

The nature of the intervention does not allow blinding of participants or personnel performing the intervention. However, the outcome assessor is blinded to the result of the randomization throughout the trial, and all data analysis is performed blinded.

## Methods: data collection, management, and analysis

### Data collection methods

Depending on the outcome, data collection is performed at baseline (t_1_), 8 weeks after discharge (t_2_), 16 weeks after discharge (t_3_), 1 year after discharge (t_1y_), and at the GFR-measurement (t_GFR_) (Tables 1 and 2).

Data collection is performed by the same assessor whenever possible to minimize variation. All assessors are provided supervised training in data collection by primary investigator [name], [name], [name], [name], or [name] until deemed ready to perform data collection unsupervised. Data are collected in the ED at baseline and in each participants’ home during follow-up. If a participant declines full data collection at follow-up, then they are offered minimal data collection consisting of blood samples, body weight, MNA-SF, EuroQol-5D-5L, blood pressure, heart rate, hand grip strength, and body composition with BIA. If the participant declines minimal data collection, then they are offered to complete any components of data collection that can be performed by telephone interview. A full medication list for each participant is recorded at every follow-up visit, and the patient’s diagnosis codes and laboratory tests are accessed in the patient chart and stored for future MAI and AOU scores assessment. A full medication list for each participant is recorded at every follow-up visit, and the patient’s diagnosis codes and laboratory tests are accessed in the patient chart and stored for future calculation of MAI and AOU scores. A self-reported medication list is obtained by a senior pharmacist through interviewing the participant, and this list is cross-referenced with the Shared Medication Card. If there are any discrepancies between medications reported by the patient and those found in the Shared Medication Card, then the senior pharmacist confirms the medications by contacting the participant’s relatives, home care personnel, or GP. Registry data (see Table 2) are obtained retrospectively.

### Data management

Procedures for data entry, coding, security, and storage have been approved by the Danish Data Protection Agency (VD-2018-390). Whenever possible, data are entered directly into REDCap (Research Electronic Data Capture, Vanderbilt University, Nashville, USA). If data are collected on paper case report forms, then a double entry in REDCap is performed. Data analysis will be performed in SAS Enterprise Guide version 9.4 M5 (SAS Institute Inc., Gary, NC, USA) and R, Version 3.6.1 (R Foundation for Statistical Computing, Vienna, Austria).

### Statistical methods

#### Primary outcomes

Differences in MAI score, change from baseline to 8 weeks after discharge between the control group and pooled intervention group (MED and MULTI-NUT-MED intervention), will be evaluated by analysis of covariance (ANCOVA). The primary analysis will model the randomization group and baseline MAI-score as independent variables by the intention-to-treat principle. Additional analyses will be adjusted for potential confounders that are unequally distributed between groups despite randomization. Missing data on the primary end point will be accounted for by multiple imputations using the PROC MI procedure with fully conditional specification (FCS) and a minimum of 100 imputations. Imputation will use earlier measurements of the imputed outcome, number of medications, and randomization group, along with age and sex for prediction models.

Differences between mGFR and eGFR based on both the combination of creatinine and cystatin C will be evaluated by mixed linear regression analysis.

The difference in EuroQol-5D-5L score change from baseline to 16 weeks after discharge between the control group and MULTI-NUT-MED intervention group will be evaluated by ANCOVA. The primary analysis will model randomization group and baseline EuroQol-5D-5L as independent variables with either intention-to-treat analysis or per-protocol analysis, where participants are considered compliant if they received and were compliant to at least one intervention if one was recommended, two if two were recommended, two if three were recommended, three if four were recommended, and four if five or six were recommended. Additional analyses will be adjusted for potential confounders that are unequally distributed between groups despite randomization. Missing data on the primary endpoint will be accounted for by multiple imputations using the PROC MI procedure with fully conditional specification (FCS) and a minimum of 100 imputations. Imputation will use earlier measurements of the imputed outcome along with age, sex, and diagnosis codes for prediction models.

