## Abstract

**Background:**

Internationally, older patients (≥65 years) account for more than 40% of acute admissions. Older patients admitted to the emergency department (ED) are frequently malnourished and exposed to inappropriate medication prescribing, due in part to the inaccuracy of creatinine-based equations for estimated glomerular filtration rate (eGFR). The overall aims of this trial are to investigate: (1) the efficacy of a medication review (MED intervention) independent of nutritional status, (2) the accuracy of eGFR equations based on various biomarkers compared to measured GFR (mGFR) based on ^99m^Technetium–diethylenetriaminepentaacetic acid plasma clearance, and (3) the efficacy of an individualized multimodal and transitional nutritional intervention (MULTI-NUT-MED intervention) in older patients with or at risk of malnutrition in the ED.

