**Methods:**

The trial is a single-center block randomized, controlled, observer-blinded, superiority and explorative trial with two parallel groups. The population consists of 200 older patients admitted to the ED: 70 patients without malnutrition or risk of malnutrition and 130 patients with or at risk of malnutrition defined as a Mini Nutritional Assessment-Short Form score ≤11. All patients without the risk of malnutrition receive the MED intervention, which consists of a medication review by a pharmacist and geriatrician in the ED. Patients with or at risk of malnutrition receive the MULTI-NUT-MED intervention, which consists of the MED intervention in addition to, dietary counseling and individualized interventions based on the results of screening tests for dysphagia, problems with activities of daily living, low muscle strength in the lower extremities, depression, and problems with oral health. Baseline data are collected upon study inclusion, and follow-up data are collected at 8 and 16 weeks after discharge. The primary outcomes are (1) change in medication appropriateness index (MAI) score from baseline to 8 weeks after discharge, (2) accuracy of different eGFR equations compared to mGFR, and (3) change in health-related quality of life (measured with EuroQol-5D-5L) from baseline to 16 weeks after discharge.

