#### Inappropriate prescribing and medication review intervention

Polypharmacy is common among older patients in part because medications are readily prescribed for new conditions, but the appropriateness of continuing each medication is rarely evaluated [20–22]. Polypharmacy and other causes of inappropriate medication prescribing may lead to adverse drug reactions, which are responsible for up to 15% of unplanned hospitalizations [23]. Therefore, dose adjustment and deprescribing of inappropriate medications are important components of medication reviews for older patients [24]. Medication optimization in older patients is challenging due to the presence of comorbidities and individual variations in age-related physiological changes including pharmacokinetic, pharmacogenetic, and pharmacodynamic responses to medications [25, 26].

Pharmacist-led medication reviews have been proposed as an important component of optimizing medication prescribing [27], but there is conflicting evidence regarding the impact and efficacy of medication reviews for older patients in the ED [28–32]. International studies have shown that collaboration between pharmacists and physicians in multidisciplinary hospital teams can decrease inappropriate prescribing among older patients in a transitional setting [33–35]. We have previously shown that a medication review in the ED is feasible and led to increased medication appropriateness between admission and discharge in 64% of the patients [36]. However, this finding has never been demonstrated among older patients in the ED using a randomized controlled trial. Therefore, we aim to use a randomized controlled trial to determine the efficacy of a medication review (MED intervention) in a cohort of acutely admitted older patients both without and with risk of malnutrition.

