### Aims

The study involving acutely admitted older medical patients has three primary aims (1) to determine whether a medication review intervention is superior to standard care in improving medication appropriateness from admission to 8 weeks after discharge, (2) to determine the accuracy of eGFR equations based on various biomarkers compared to mGFR at a single-time point, and (3) to determine whether an individualized multimodal and transitional nutritional intervention is superior to standard care in improving the quality of life from admission and 16 weeks after discharge.

The study also has the following secondary aims which are related to the effect of the intervention: (1) to measure differences in polypharmacy, PIM use, and assessment of underutilization between the MED-intervention and standard care from admission to 8 weeks after discharge and (2) to measure of the differences in body weight, protein- and energy intake, mobility, cognition, frailty, the intestinal microbiome, and health care costs between the MULTI-NUT-MED intervention and standard care from admission to 8 and 16 weeks after discharge and 1 year after discharge (only health care costs).

Secondary aims, which are based on baseline data or data from the control group, include assessment of (1) how information from a broad pharmacogenetic test can potentially improve medication prescribing appropriateness; (2) how polypharmacy, PIMs, nutritional status, frailty, and inflammation modify the effect of the MED-intervention on prescribing appropriateness; (3) how non-GFR determinants affects eGFR and how the choice of eGFR equation affects medication prescribing; (4) how the choice of malnutrition classification criteria affects the prevalence of malnutrition; and (5) how different definitions of frailty affect the distribution of patients classified as frail or sub-frail as well as the responsiveness of these methods.

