##### After discharge

Prior to discharge, a dietary plan for the first week after discharge is created based on the participant’s food preferences, nutritional needs (evaluated by the Nordic Nutrition Recommendations [75] with an optional stress factor), ability to chew (pain in their mouth, difficulties chewing) and swallow (evaluated by the EAT-10 score [71, 72] and an occupational therapist), and limitations in grocery shopping, cooking or eating (evaluated by the Functional Recovery Score (FRS) [76]). If ONS is a part of the dietary plan after discharge, then the participant is provided with an ONS prescription, which can be filled at the pharmacy with a 60% price reduction. At discharge, the dietary plan is provided to both the participant and community-based dietician.

Participants are offered 1-h home visits by the community-based dietician at 1, 2, 4, and 8 weeks after discharge to evaluate changes in body weight and energy and protein intake and to adjust the dietary plan if needed. If a participant is readmitted within 16 weeks of discharge, they are offered dietary counseling during rehospitalization.

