##### Evaluation of depression and treatment

Participants are screened during baseline data collection for depression using the Mini Geriatric Depression score [88]. Participants with a Mini Geriatric depression score ≥2 are subsequently screened with the Geriatric Depression Score-15 (GDS-15) [89]. Participants with a GDS-15 ≥5 are offered evaluation and treatment for depression by a geriatrician during hospitalization. After discharge, the geriatrician can follow up on treatment by phone. If the participant is discharged before evaluation and treatment by the geriatrician, then they are recommended to see their GP.

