### Sample size

The trial has three primary endpoints that build on mutually independent hypotheses [140]. Therefore, sample size calculations were performed for each endpoint as described below. All sample size calculations are performed for a significance level of 5%, power of 80%, and a dropout rate of 25%. Ethical approval was obtained for the inclusion of 200 participants in total to ensure enough power for all primary endpoints.
1: Based on a *t* test, a sample size of 120 is required to detect a clinical difference of 3 points (SD=5 points [36]) in MAI score change from baseline to 8 weeks after discharge between the control group and pooled intervention group (MED and MULTI-NUT-MED intervention).2: Based on a paired *t* test, a sample size of 62 participants is required to detect a clinically relevant difference of 4.0 mL/min/1.73m^2^ (SD=15, a R=0.73 [141]) between mGFR and eGFR based on the combination of creatinine and cystatin C. GFR is measured at baseline for all trial participants regardless of group allocation.3: Based on a *t* test, a sample size of 130 participants with or at risk of malnutrition is required to detect a clinically relevant difference of 0.15 points [142] (SD=0.27 [143]) in EuroQol-5D-5L score change from baseline to 16 weeks after discharge between the control group and MULTI-NUT-MED intervention group, assuming equal allocation in the two groups.

Given that patients are included independently of nutrition status and approximately 70% of patients are expected to have or be at risk of malnutrition [4], a total of 185 participants is required to achieve a sample size of 130 participants with or at risk of malnutrition.

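### The pooled MAI contrast estimates medication review with or without the nutritional package, not the medication review alone that aim 1 names

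*Protocol article*

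**What the plan says.** The Abstract gives aim 1 as "the efficacy of a medication review (MED intervention) independent of nutritional status". The Aims section asks the trial "to determine whether a medication review intervention is superior to standard care in improving medication appropriateness from admission to 8 weeks after discharge". The Introduction places the question "in a cohort of acutely admitted older patients both without and with risk of malnutrition".

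Under Interventions, intervention-arm patients with MNA-SF >11 receive the review only (MED). Those with MNA-SF ≤11 receive MULTI-NUT-MED, which is the review plus dietary counseling, occupational therapy, physiotherapy, depression evaluation and treatment, and oral health care. Under Standard care, controls receive standard care only, whatever their nutritional status. The Abstract plans "70 patients without malnutrition or risk of malnutrition and 130 patients with or at risk of malnutrition".

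Some added elements can reach the medication list or bring prescriber contact before week 8, when need is found:
- Depression: "Participants with a GDS-15 ≥5 are offered evaluation and treatment for depression by a geriatrician during hospitalization", with telephone follow-up possible.
- Oral nutritional supplements (ONS), if they are in the discharge plan: "then the participant is provided with an ONS prescription, which can be filled at the pharmacy with a 60% price reduction".
- Oral health: antifungal treatment where candidiasis is suspected and treatment is needed.

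Under Statistical methods, Primary outcomes, the change in MAI "between the control group and pooled intervention group (MED and MULTI-NUT-MED intervention), will be evaluated by analysis of covariance (ANCOVA"). The primary model contains randomization group and baseline MAI. Additional analyses adjust for confounders found to be unequally distributed. Randomization is stratified by age, sex and municipality, not by MNA-SF.

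**The concern.** The aim names one intervention and the contrast tests two. In the larger stratum, review and package always come together and are compared with neither. If the pooled result is positive, a reader of the aim will take it as evidence for a pharmacist and geriatrician review in the emergency department. Most of that evidence would come from patients also assigned a much broader and costlier programme.

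Aim 3 has the same labelling problem in reverse. The Aims section calls the intervention nutritional, but every recipient also gets the medication review, and the Introduction links polypharmacy to lower quality of life.

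The secondary aim on nutritional status as a modifier of the review's effect does not resolve this. The Aims section lists it among aims based on baseline or control-group data, and such data cannot show how a treatment effect varies.

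**Working it through.** **Inputs.** Sample size section: difference 3 points, SD 5, 5% significance (taken as two-sided; the article does not say), 80% power, 25% dropout, stated N = 120. Abstract: 70 and 130 of 200. Allocation section: 1:1.

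**The plan's own figure.** Normal approximation: n per arm = 2(1.96 + 0.84)² × 5²/3² ≈ 43.6, so 44. The t-test version gives 44.6, so 45 per arm; 90/0.75 = 120. The stated figure reproduces, and it is for the pooled contrast.

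**Share assigned the package.** 130/200 = 65%. The Sample size section also says that "approximately 70% of patients are expected to have or be at risk of malnutrition", and 130/185 = 70.3%. The realised share can move, because the recruitment rules allow days on which only one MNA-SF group is enrolled.

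**What the pooled contrast estimates.** Let x be the effect of the added package on MAI change in the MNA-SF ≤11 stratum. Then

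pooled effect = average effect of the review + 0.65x.

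The documents give no value for x. As an assumption only:

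| x (points) | shift in pooled estimate | share of the 3-point target |
|---|---|---|
| ±0.5 | ±0.33 | 11% |
| ±1 | ±0.65 | 22% |
| ±2 | ±1.3 | 43% |

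**What the MNA-SF >11 stratum can say.**
- n = 70 × 0.75/2 = 26.25, about 26 per arm.
- SE = 5√(2/26) = 1.39.
- 95% half-width (t, 50 df) = 2.01 × 1.39 ≈ 2.8 points.
- Power for 3 points = 56% (57% at 26.25 per arm).
- Difference detectable with 80% power ≈ 3.9 points.
- With no dropout (35 per arm), power is about 70%.
- With 185 − 130 = 55 such patients and 25% dropout, power is about 47%.
- On the trial's inputs, 120 patients would be needed here, against 70 planned.

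**Can comparing strata recover x?** No. All package recipients have MNA-SF ≤11 and all review-only recipients have MNA-SF >11, so package and nutritional status are fully confounded. The comparison is also imprecise. With 48.75 and 26.25 per arm, SE = 5√(2/48.75 + 2/26.25) = 1.71, and the detectable difference is about 2.80 × 1.71 = 4.8 points.

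**The case against.** The strongest defence is that aim 1 means the review's effect *regardless of* nutritional status. The Introduction and the Sample size section support this, the latter saying that patients enter independently of nutrition status. The pooling is disclosed wherever the contrast is described, and the sample size was set for it. All of this stands. It justifies the population and the test, but does not make the package part of the review.

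Four stronger readings should be resisted:

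- **That 65% of the intervention arm get new prescriptions or extra prescriber contact.** They are assigned a package that may bring these. Depression care needs two positive screens, ONS must be in the discharge plan, and antifungals require suspected candidiasis and need. The share affected is unknown and is likely to be lower. The review itself also looks for undertreated conditions, so part of this overlaps with MED.
- **That the pooled result is biased in a known direction, or could be driven to null.** MAI scores inappropriateness, so an indicated new drug need not raise it. The article does not say whether ONS is scored.
- **That the plan ignores nutritional status, or certainly plans no stratum estimate.** The modifier aim is stated, although its stated data basis cannot serve it. The article's Statistical methods give no MAI estimate by stratum, but a fuller analysis plan might. The point rests on the stated aim against the stated contrast, not on an omission.
- **That 80% power is claimed for the review alone.** The article makes no such claim. The 56% describes what the isolating stratum can deliver and is not an error in the sample size.

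On aim 3, the acronym and definition of MULTI-NUT-MED do disclose the review as a deliberate component. What remains there is the wording of the aim and its conclusion.

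**Conclusion.** The point holds as one of attribution. The pooled intention-to-treat comparison is sound for *medication review with or without the nutritional package* against standard care. It does not identify the effect of the review alone, because 65% of planned participants (about 70% under the expected natural mix) are in a stratum with no review-only assignment.

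The size of the resulting discrepancy cannot be computed, since the documents give no package effect on MAI; the shifts tabulated above are illustrations. The only randomized estimate of the review alone is in MNA-SF >11, with a half-width of about 2.8 points against a 3-point target. That figure assumes SD 5 in this stratum, 25% dropout, equal arms, and precision close to that of completers. Baseline adjustment might narrow it, but the article gives no correlation from which to say by how much.

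**What to change.** 1. Keep the pooled MAI comparison as the primary test.
2. Add baseline MNA-SF stratum (≤11 / >11) as a covariate in the MAI ANCOVA.
3. Prespecify the group effect with a 95% interval within each stratum, as supportive estimates.
4. Attribute an effect to medication review alone only from the MNA-SF >11 estimate, and state its imprecision beside it. State that any difference between strata confounds the package with nutritional status.
5. Word the aim 1 conclusion as the effect of medication review with or without the nutritional package, and the aim 3 conclusion as the effect of the combined nutrition-plus-medication-review package.

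Do not add a sensitivity MAI that leaves out items started by the package. The same items started in usual care would stay in for controls, so the exclusion would be asymmetric and made after randomization.

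The cost is analysis code and wording. MNA-SF is already collected at baseline in all participants by assessors blinded to allocation, so no further data or patients are needed. The downside is a narrower headline claim and a stratum estimate that may well be inconclusive.
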